## Methods and analyses

### Design and setting

This is the version of the protocol, dated 1 April 2023. The study protocol was designed in accordance with standard protocol Items: Recommendations for Interventional Trials (6) (Supplementary File 1). The study protocol was approved by the Ethics Committee of IRB of The First Teaching Hospital of Tianjin University of TCM (TYLL2023[K]031). The study will be conducted in the First Teaching Hospital of Tianjin University of Traditional Chinese Medicine. In this study, 40 patients with post-stroke limb dysfunction and 20 healthy people will be included, and patients will be randomized into 2 groups in 1:1 ratio. The intervention group will receive XNKQ acupuncture therapy and basic therapy, the control group only will receive basic therapy. Acupuncture treatment will be given 6 times a week for 2 weeks. Outcome indicators include clinical scales and imaging indicators. Healthy people will be accessed at baseline, patients will be evaluated at baseline and after 2 weeks. The flow chart of this study is shown in Figure 1. The schedules of this study is shown in Table 1.

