### Inclusion criteria

The inclusion criteria are as follows:

1. Patients group:Meets the above diagnostic criteria;First-ever clinical CIS occurred ≤2 weeks, the number of times ≤ 1;40–70 years old, right-handed;Unilateral basal ganglia infarction and the area of infarction is 3.0 ~ 5.0 cm in diameter at the largest level, with motor dysfunction and manual muscle testing showing muscle strength grades 1 to 4;No severe cognitive impairment and also mini-mental state examination (MMSE) with a score of 17 or above.Provided written informed consent to participate.

2. Healthy people groupAge and sex were matched with the patient group, right-handed;Subjects are in good health and free of organic and significant functional diseases;No previous family history of the mental and nervous system;No stimulant drugs have been taken in the past 2 months;Provided written informed consent to participate.

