### Primary outcomes

Blood oxygen level-dependent functional magnetic resonance imaging (BOLD-fMRI) indirectly evaluates neuronal activity by monitoring changes in blood oxygenation (10). Amplitude of low frequency fluctuation (ALFF) and regional homogeneity (ReHo) are common evaluation indicators (11). ALFF represents the spontaneous activity of neurons, and its derivative, fraction amplitude of low frequency fluctuation (fALFF), can better remove noise signals such as heartbeat and respiration, and is more sensitive and precise. ReHo responds to intervoxel activity synchronization by calculating the consistency of voxels over time series. The two indicators have better repeatability and clear physiological significance. Functional connectivity (FC) reflects functional integration between regions.

Voxel-based morphometry (VBM) is a structural MRI quantitative analysis technique in which gray matter volume or gray matter density can be obtained by calculating the gray matter.

Diffusion tensor imaging (DTI) technique traces fiber bundle alignment and identifies structural changes in white matter fibers (12), and fractional anisotropy (FA) is the most commonly used measure reflecting the integrity of white matter fiber bundles (13).

Arterial spin labeling (ASL) is a magnetic resonance perfusion imaging technique that can be used to detect cerebral blood perfusion (14). As an important indicator, cerebral blood floot (CBF) can reflect cerebral blood flow perfusion (15).

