### Data collection and statistical analysis

Data will be collected using the paper CRFs which will be kept in a locked cabinet at the end of the trial. Statistical analysis of data will be performed by an independent researcher. For dislocated subjects, we will record the number and reason for termination, especially adverse events. Data will be analyzed using the R software version R-4.2.2. Statistical significance is defined as a *p* value of <0.05.

For comparisons of baseline material, measurements that follow a normal distribution overall will be expressed as mean ± standard deviation (
$\bar{X}$
 ± SD), and the whole data that do not follow a normal distribution will be expressed as median (interquartile range, IQR) [M (P25-P75)]. Count data will be expressed as the number of cases (n) and percentage (%) using the X^2^ test. The *t*-test or Mann–Whitney U-test will be chosen to compare the two groups’ scores on each scale based on a normal distribution and homogeneous variance. For within-group comparisons, changes in scores will be assessed by paired *t*-test or Wilcoxon rank-sum test. For subjects who discontinued or deviated from the intervention, listwise deletion or multiple interpolation will be used.

The multimodal MRI images will be analyzed by MATLAB 2023a and the statistical parameter graph software Statistical Parametric Mapping (SPM)12. Before data processing, all data will be removed the first 10 time points to retain the stabilized images; and adjust for differences arising from the time points, after which orientation alignment will be performed; and all aligned functional images will be aligned to the montreal neurological institute (MNI) space with a voxel standard size of 3 mm × 3 mm × 3 mm, and then the functional images will be smoothed with a Gaussian kernel of 6 mm × 6 mm × 6 mm. Afterward, the images will be datamined by extracting the indicators. Data will be analyzed with two independent samples *t*-tests to compare the differences between the patient group before treatment and the healthy group, as well as the differences between the acupuncture group and the no-acupuncture group after treatment. The longitudinal changes in MRI indexes before and after the respective treatments of the two groups of patients will be observed with paired *t*-tests. Age, gender, BMI, blood pressure, and history of diabetes will be used as covariates in data analysis.

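### The functional-image steps and the covariate list take no account of the infarct, so the patient-versus-healthy maps can show the lesion itself and the within-arm changes mix its evolution with treatment

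*Protocol article*

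**What the plan says.** Three sections of the protocol article bear on this point.

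- **Inclusion criteria.** Patients have a "Unilateral basal ganglia infarction" for which "the area of infarction is 3.0 ~ 5.0 cm in diameter at the largest level", and "First-ever clinical CIS occurred ≤2 weeks". A sizeable, recent lesion is therefore a condition of entry.
- **Design and setting.** "patients will be evaluated at baseline and after 2 weeks". If eligibility and the baseline scan coincide, the infarct is up to about 14 days old at the first scan and up to about 28 days at the second.
- **Data collection and statistical analysis.** The functional steps come in order: the first 10 time points are dropped, timing is corrected, images are aligned, "all aligned functional images will be aligned to the montreal neurological institute (MNI) space" at a voxel size of 3 mm on each side, a 6 mm Gaussian kernel is applied, and indices are extracted. Three kinds of t-test follow: patients before treatment against healthy people (two-sample), the two arms after treatment (two-sample), and before against after within each arm (paired). The covariates named are age, gender, BMI, blood pressure and diabetes history.

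No section mentions a lesion mask, lesion-adapted normalisation, exclusion of infarcted voxels, or infarct size as a covariate.

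**The concern.** The trial is meant to show a central mechanism of acupuncture. That requires separating the infarct from the response of the surviving brain, and the three contrasts are exposed differently.

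- **Patients against healthy people.** Only one side has an infarct. If infarcted voxels stay in the template fit and the tests, the infarct, and tissue blended with it by smoothing, can appear as altered ALFF, ReHo or connectivity.
- **Before against after, within an arm.** A recent infarct can be expected to change over two weeks whatever the treatment. A significant change in the acupuncture arm then has two explanations that the test cannot separate. Significant indices from that arm also go forward to correlation with its clinical scores.
- **Arm against arm, after treatment.** Randomisation protects this contrast on average. What remains is avoidable noise and the chance that one small arm has larger infarcts, with neither infarct size nor the baseline MRI value among the covariates.

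**Working it through.** **The plan's own figure.** The Sample size section takes 16 evaluable per group and 20% dropout: 16 / (1 − 0.20) = 20 per group, as stated. The calculations below use 16 and 20.

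**Extent of the infarct.** Only a largest diameter is given, so a sphere is assumed: volume = (π/6)d³. The planned voxel is 3 × 3 × 3 = 27 mm³.

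- d = 3 cm: 14.1 mL, about 524 voxels.
- d = 5 cm: 65.4 mL, about 2,424 voxels.
- Ratio: (5/3)³ = 4.6 among eligible patients.

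The 6 mm kernel is 6/3 = 2 voxels wide, so functional values at the infarct edge are averaged with neighbouring tissue.

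**Patients against healthy people.** Infarct size is zero in every healthy person, so it is tied to group membership. A size covariate cannot separate lesion from response here; only keeping infarcted voxels out can.

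**Within-arm paired tests.** Assume no acupuncture effect and a spontaneous change of δ SD of the differences, equal in both arms. The documents give no value, so a range is shown. The test statistic is noncentral t with n − 1 degrees of freedom and noncentrality δ√n, two-sided 5%. If P is the probability of significance, the probability that the acupuncture arm is significant and the control arm is not is P(1 − P).

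| δ | n | P | P(1 − P) |
|---|---|---|---|
| 0.3 | 16 | 20% | 16% |
| 0.5 | 16 | 47% | 25% |
| 0.8 | 16 | 85% | 13% |
| 0.3 | 20 | 25% | 19% |
| 0.5 | 20 | 57% | 25% |
| 0.8 | 20 | 92% | 7% |

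**Arm against arm, after treatment.** 

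1. Type I error: 40,000 simulated trials with 16 per arm, no treatment effect, and a correlation of 0.3, 0.5 or 0.7 (assumed) between infarct size and index gave 4.9%, 5.1% and 4.8%. The test keeps its level.
2. Chance imbalance: the standard error of a standardised difference in mean infarct size is √(2/n). At n = 16, 0.5/0.354 = 1.41, so a difference above 0.5 SD has probability 16%. At n = 20, 0.5/0.316 = 1.58, so 11%.
3. In the simulated trials with such an imbalance, the false-positive rate was 7.5%, 12% and 18% for correlations 0.3, 0.5 and 0.7.
4. In millilitres, with diameters uniform on 3 to 5 cm (assumed): mean volume 35.6 mL, SD 14.8 mL. The 95% range of the chance difference between arms is ±1.96 × 14.8 × √(2/16) = ±10.3 mL, or ±9.2 mL with 20 per arm.
5. Precision: adjusting for infarct size multiplies residual variance by about 1 − r², that is 0.91, 0.75 and 0.51 for r = 0.3, 0.5 and 0.7, less the small cost of one degree of freedom.

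**The case against.** The strongest reply is that this is a condensed article. It gives no frequency band for ALFF, no seeds for connectivity and no tensor fitting, all of which the primary outcomes need. A lesion mask may sit in the same unshown document. That stands in part: a reader might infer that infarcts will be processed as normal brain tissue, but nothing in the article says so. The missing mask is partly silence. The covariate list is not: it is stated, and infarct size is not in it.

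The second objection concerns scope. The normalisation sentence covers functional images. The article defines VBM by saying that "gray matter volume or gray matter density can be obtained by calculating the gray matter", but does not describe spatial processing of T1, DTI or ASL images. A faulty template fit for grey matter volume, FA or CBF cannot be read from the text. This stands.

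Third, a reader might infer that infarct size and evolution would pass as an acupuncture effect in the randomised comparison. The documents do not support that: both arms come from one eligibility range by 1:1 randomisation, and the simulated error rate stays near 5%. A chance imbalance is already allowed for in the standard error. Adjustment improves precision and guards against the unlucky allocation; it does not correct a bias.

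Fourth, entry is already narrowed to a first, unilateral infarct at one site within a size band. True, but the band still spans a 4.6-fold range of volume under the sphere assumption. The infarct is also local, so voxels elsewhere remain informative. Finally, masking would not rescue the paired tests, because surviving tissue also changes on its own. That is accepted and shapes the fix.

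**Conclusion.** The point holds in a limited form.

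- **Patients against healthy people:** exposed at and near the infarct, with no protection from randomisation. Firm for the BOLD indices if the steps are applied as written; open for the structural, diffusion and perfusion images.
- **Within-arm paired tests:** not interpretable as a treatment effect. With spontaneous change of 0.3 to 0.8 SD and no acupuncture effect, the acupuncture arm alone is significant in 13% to 25% of trials at 16 per arm.
- **Randomised arm contrast:** valid on average. The loss is precision, plus a 16% (16 per arm) or 11% (20 per arm) chance of an imbalance above 0.5 SD.

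This rests on assumptions, because the documents give no values: spherical infarcts, the sizes of spontaneous change, the correlations between infarct size and index, and two-sided tests. That infarcts evolve over the two weeks is general knowledge, not a statement of the article. Voxelwise testing is inferred from the use of SPM12, from VBM and from the single-voxel basis of the sample size. The ±10.3 mL and ±9.2 mL figures describe imbalance in infarct size, not an error in an MRI index.

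**What to change.** Change the analysis section in three places.

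1. Add baseline infarct size to the covariates of the arm comparison. The diameter already assessed for eligibility will do, or a volume from the T1 and diffusion images already acquired.
2. State that an infarct mask, drawn blind to arm by the existing analyst, is excluded from the functional normalisation fit and from the tested voxels, and say how voxels missing in some patients are handled. This last rule matters because either side is eligible, and a mask pooled over patients could remove much of the basal ganglia on both sides. If masking is already planned, one sentence confirming it is enough. The same sentence should say whether it covers the T1, DTI and ASL images.
3. State that within-arm paired changes are descriptive and will not be read as an acupuncture effect; that question belongs to the comparison between arms.

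The cost is about 80 masks (40 patients at two time points), no inference inside the infarct, and a sixth covariate in a small sample. No extra scan, visit or patient is needed.

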### Data acquisition

Data will be acquired by a Siemens Skyra 3.0 T MRI scanner (Siemens Healthineers) equipped with a 32-channel head coil. For BOLD-fMRI images, we used an echo-planar imaging (EPI) sequence (repetition time (TR) = 2,000 ms, echo time (TE) = 30 ms, flip angle = 90°, matrix = 64 × 64, field of view (FOV) = 220 mm × 220 mm, resolution = 3.4 × 3.4 × 3.0 mm^3^, gap = 0.99 mm, 240 time points, 37 interleaved axial slices). The structural image of the whole brain will be acquired for each participant using the T1 sequence (TR = 2,000 ms, TE = 1.97 ms, FOV = 256 mm × 256 mm, matrix = 192 × 192, voxel size = 1 × 1 × 1 mm^3^). White matter fiber bundle structure will be acquired from the DTI sequence (voxel size = 2 × 2 × 2 mm^3^, TE = 75 ms, TR = 8,200 ms, 70 slices, matrix = 110 × 110, FOV = 220 × 220 mm^2^, b = 0,1,000 s/mm^2^, and 64 diffusion directions). The cerebral perfusion imaging will be acquired by ASL sequence (TR = 4,000 ms, TE = 16.18 ms, matrix = 64 × 64, FOV = 220 × 220 mm^2^, voxel size = 3.4 × 3.4 × 3.0 mm^3^ TI1/TI = 700/1990 ms). Subjects’ heads will be immobilized by cushioned supports, and they will wear earplugs to protect against MRI gradient noise throughout the experiment.

For the observation steps, we will communicate with the patient in advance about the length of the scanning, so that the patient will not feel anxious if the time is too long. The subject’s ears will be plugged with cotton balls. When the patient is ready, the patient’s entire brain will be scanned. During resting-state scanning, patients will be instructed to relax, close their eyes, remain still, and avoid thinking activities as much as possible.

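### ReHo is extracted after 6 mm smoothing, which inflates the local synchrony it measures and can blunt true differences

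*Protocol article*

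**What the plan says.** The preprocessing paragraph of the protocol article (Data collection and statistical analysis) gives a sequence. The images are resampled in MNI space to isotropic voxels of 3 mm. Smoothing is the step after that: "then the functional images will be smoothed with a Gaussian kernel", whose width is given as 6 mm in each direction. Extraction of the indices comes last: "Afterward, the images will be datamined by extracting the indicators". The connecting words fix the order, and no index is given a separate, unsmoothed branch.

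Under Primary outcomes the article states "Amplitude of low frequency fluctuation (ALFF) and regional homogeneity (ReHo) are common evaluation indicators" and describes the second of them thus: "ReHo responds to intervoxel activity synchronization by calculating the consistency of voxels over time series".

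The extracted indices then enter two-sample t-tests (patients against healthy people before treatment; acupuncture against no acupuncture after it) and paired t-tests within each arm. Significant values from the acupuncture arm are correlated with clinical scores.

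**The concern.** A Gaussian filter replaces each voxel's time series by a weighted average of its own and its neighbours' series. Neighbouring voxels then share part of their data whether or not the underlying activity was synchronous. ReHo asks how far neighbouring voxels move together, so in the stated order the filter supplies part of the quantity before it is measured.

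This does not carry over in the same way to ALFF or fALFF, which measure amplitude, or to FC, which measures integration between regions.

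At stake is the interpretability and sensitivity of one listed primary index. If ReHo showed no difference, the reader could not tell absence of effect from a blunted measure. The sample size section plans on 16 evaluable subjects per group, which leaves little sensitivity to spare.

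**Working it through.** **Inputs from the article.** Voxels are 3 mm and the kernel is 6 mm (Data collection and statistical analysis). Acquisition is "240 time points, 37 interleaved axial slices" (Data acquisition), and "all data will be removed the first 10 time points" leaves 240 − 10 = 230 time points. The article reports no ReHo value, so it has no figure of its own to reproduce.

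**Assumptions not in the article.** 6 mm is the full width at half maximum (FWHM); ReHo is Kendall's W over 3 × 3 × 3 = 27 voxels; signal share and signal width are varied below.

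**Step 1: correlation imposed on pure noise.** σ = 6/2.3548 = 2.548 mm, so 4σ² = 25.97 mm². For independent noise smoothed with this kernel, the correlation at distance d is exp(−d²/4σ²):
- face neighbours, d² = 9: 0.71
- edge neighbours, d² = 18: 0.50
- corner neighbours, d² = 27: 0.35

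**Step 2: Kendall's W.** With mean rank correlation r over the 27 voxels, W = r + (1 − r)/27.
- Unsmoothed, r = 0: W = 1/27 = 0.037.
- Smoothed, r ≈ 0.312: W = 0.312 + 0.688/27 = 0.337. Simulation with 230 time points gave 0.33 to 0.34.

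The smoothed value would be 0.16 with a 4 mm kernel, 0.50 with 8 mm, and about 0.77 if 6 mm were σ. The direction does not depend on the FWHM reading.

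**Step 3: allowance for resampling.** The images are acquired at 3.4 × 3.4 × 3.0 mm with a 0.99 mm gap and resampled to 3 mm, and interpolation alone correlates neighbours. Simulated with an assumed small rotation, W in noise before smoothing is 0.08 (cubic) to 0.14 (linear), and 0.36 to 0.42 after. The ratio is 0.42/0.14 = 3.0 to about 4.4 (0.36/0.08 in rounded figures), not the 0.337/0.037 ≈ 9 of step 2.

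**Step 4: noise plus a spatially limited signal.** W unsmoothed → smoothed, for three assumed signal widths (Gaussian σ in voxels):

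| Signal share | 1.0 | 1.5 | 2.5 | (smoothed − unsmoothed)/smoothed |
|---|---|---|---|---|
| 20% | 0.11 → 0.52 | 0.16 → 0.64 | 0.20 → 0.78 | 75–78% |
| 40% | 0.19 → 0.55 | 0.28 → 0.69 | 0.35 → 0.83 | 57–66% |
| 60% | 0.27 → 0.57 | 0.40 → 0.70 | 0.51 → 0.84 | 39–52% |
| 80% | 0.35 → 0.57 | 0.53 → 0.71 | 0.67 → 0.85 | 21–40% |

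The last column is the rise on filtering as a share of smoothed W. It is not all artefact, because averaging also removes noise and uncovers signal that really is shared. Raising the signal share from 40% to 80% moves unsmoothed W by 0.16 to 0.32 and smoothed W by 0.02 to 0.03.

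**Step 5: standardised difference.** A t-test depends on the difference relative to the SD, and smoothing shrinks the SD as well. With 40 simulated subjects per group and an assumed between-subject SD in signal share of 0.08 or 0.10, the standardised difference d changed as follows:
- Signal identical in all voxels: 1.13 → 1.08 (share 0.2 against 0.3) and 1.38 → 1.41 (0.4 against 0.5), about unchanged.
- Spatially limited signal: 1.44 → 0.87 (−40%), 1.18 → 0.96 (−19%), 1.59 → 1.23 (−23%), 0.85 → 0.70 (−18%).
- A further pair of simulations with spatially limited signal: 1.23 → 1.11 (−10%) and 1.03 → 0.81 (−21%).

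These are small simulations under assumed settings. They support a direction and a rough size, not the second decimal.

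**Step 6: scale.** Information for a t-test goes roughly with n·d². A 10% loss in d makes 16 subjects per group worth about 16 × 0.9² = 13. The extreme 40% loss makes them worth about 16 × 0.6² = 6. Under a fully common signal nothing is lost.

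**The case against.** Several objections have force.

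- **Between-arm bias.** A reader might infer that the filter could produce a spurious acupuncture effect. The documents do not support this: one pipeline serves all groups and visits, so the filter alone creates no difference between arms.
- **ReHo as mainly a product of the filter.** This is a tempting inference from the pure-noise figure, but brain data are not pure noise. Step 4 shows the rise ranging from 21% to 78% of the smoothed value depending on signal share, and part of that rise is real signal uncovered by averaging. The article gives no signal share, neighbourhood size or ReHo value, so the share due to the filter cannot be established.
- **Narrowing of W as lost power.** A narrower range of W is not itself a loss of discrimination. Step 5 shows almost none under a fully common signal.
- **The nine-fold ratio.** It needs independent noise on the 3 mm grid, which resampling already rules out. Unsmoothed but normalised ReHo would not sit at 0.037 either.
- **Condensed text.** The paragraph is loosely worded: dropping initial time points from all data cannot literally apply to a T1 image. Index-specific processing is often left to a fuller document.
- **Scope.** ReHo is one of about seven indices under Primary outcomes.

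The first four limit the size of the claim, and all of them stand. The fifth stands only in part: the article does more than omit detail, since it states an order, and that order is unsuitable for an index it names. The sixth confines the point to ReHo.

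**Conclusion.** The point holds in a limited form. Followed as written, the paragraph computes ReHo on smoothed images, and this artificially raises local synchrony. W in independent noise goes from about 0.04 to 0.34 (6 mm as FWHM, 27 voxels), or rises about 3- to 4-fold once resampling is allowed for. It can also blunt true differences, by roughly 10–40% of the standardised difference under assumed spatially limited signals and by about nothing under a fully common one.

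The noise result is robust to kernel width in direction. The loss of discrimination depends on the model. The documents support neither a claim of bias between arms nor a statement of how much of ReHo the filter would create. The matter concerns ReHo only and should be corrected, because the stated order can only contaminate this index and the remedy is easy.

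**What to change.** In the preprocessing paragraph of Data collection and statistical analysis, replace the single sequence by two branches:

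- **ReHo:** compute it on the normalised, unsmoothed time series, then smooth the resulting ReHo map with the same 6 mm kernel.
- **ALFF, fALFF and FC:** keep the stated order, with smoothing before extraction.

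If the team already processes ReHo this way, the paragraph misdescribes the practice and one added sentence corrects it.

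The cost is one reordered step in the image pipeline and a short text change. No new scans or subjects are needed, and scans already acquired can be reprocessed. The change is best recorded before any ReHo comparison between groups is examined.

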### Outcome measures

The study period is 2 weeks. Patients in both groups will be evaluated at baseline and week 2, the healthy individuals only at enrollment. All outcomes will be measured by evaluators who will be blinded to group allocation. All evaluators will receive the same training on these evaluations.

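### The between-arm MRI test is not adjusted for the baseline value of the index, and change from baseline is tested only within each arm

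*Protocol article*

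**What the plan says.** All statements below are in the protocol article.

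- **Data available.** Under Outcome measures: "Patients in both groups will be evaluated at baseline and week 2, the healthy individuals only at enrollment". Table 1 schedules every scale and the imaging at both times.
- **MRI between arms.** Data collection and statistical analysis uses independent-samples t-tests for patients before treatment against healthy people, "as well as the differences between the acupuncture group and the no-acupuncture group after treatment".
- **MRI change.** "The longitudinal changes in MRI indexes before and after the respective treatments of the two groups of patients will be observed with paired" t-tests.
- **Covariates.** "Age, gender, BMI, blood pressure, and history of diabetes will be used as covariates in data analysis". The baseline value of the index is not listed, and the sentence does not say which tests use the covariates.
- **Scales between arms.** A t-test or "Mann–Whitney U-test will be chosen to compare the two groups’ scores on each scale based on a normal distribution and homogeneous variance". No time point is given.
- **Scales, change.** "For within-group comparisons, changes in scores will be assessed by paired" t-test or a Wilcoxon test. Change appears only here.
- **Follow-on step.** The closing paragraph of the section takes MRI indices that reached significance, in the acupuncture arm, into Pearson correlation with that arm's clinical scores.

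No ANCOVA, between-arm comparison of change or group-by-time term is stated.

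**The concern.** The Discussion sets the aim as evaluating the brain mechanism of acupuncture in comparison with no acupuncture. Only a between-arm contrast can answer that. As written, this contrast uses week-2 images without the baseline value of the same index, which has been collected and may predict the week-2 value well. Precision is lost in a study planned on 16 evaluable patients per arm.

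The analyses that do use each patient's baseline are the paired tests. Patients enter within 2 weeks of a first stroke, and both arms receive basic treatment, so change without acupuncture is plausible in both. A significant paired test in the acupuncture arm does not distinguish acupuncture from that recovery. The correlation step adds to the risk: its wording permits indices to be chosen on the acupuncture arm's own paired test.

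The tests and covariates are named in the article, so this is a stated choice and not a detail left to an analysis plan.

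**Working it through.** **The plan's own figure.** Sample size takes 16 evaluable per group and 20% dropout: 16 / (1 − 0.20) = 20 enrolled per group. This reproduces. The 16 comes from custom in the literature and carries no effect size or SD, so the inputs below marked as assumed are not in the documents.

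**Inputs.** n = 16 per arm and significance level 0.05 (from the article); two-sided testing (assumed); true difference d = 0.8 SD (assumed); correlation ρ between baseline and week-2 values of 0.3 to 0.8 (assumed).

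**1. Precision of the between-arm test.** Adjusting for baseline multiplies the residual variance by 1 − ρ². Power comes from the noncentral t with noncentrality d·√(n/2) / √(1 − ρ²). The degrees of freedom are 30 for the week-2 t-test and 29 with baseline added.

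| Analysis | Variance factor | Power at 0.8 SD |
|---|---|---|
| Week-2 values only | 1.00 | 59% |
| Baseline-adjusted, ρ = 0.3 | 0.91 | 63% |
| ρ = 0.5 | 0.75 | 71% |
| ρ = 0.7 | 0.51 | 86% |
| ρ = 0.8 | 0.36 | 95% |

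**2. Allowance for the planned covariates.** The 59% has no covariates. If the five listed ones explain an assumed 10% to 30% of the variance, the factor is 0.90 to 0.70 on 32 − 2 − 5 = 25 degrees of freedom, and power under the stated plan is 63% to 74%. The baseline value then adds only what it explains beyond those covariates.

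**3. Chance imbalance.** The SD of the baseline difference between arms is √(2/16) = 0.35 outcome-SD. A difference above 0.5 SD in either direction arises in about 16% of trials per measure. It enters the week-2 difference multiplied by ρ: a 0.35 SD imbalance shifts the estimate by 0.7 × 0.35 = 0.25 SD at ρ = 0.7, and by 0.3 × 0.35 = 0.11 SD at ρ = 0.3.

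**4. Paired tests when the arms do not differ.** Let both arms truly change by δ. The standardised change is δ / √(2(1 − ρ)), tested with 15 degrees of freedom, giving power p in each arm. The acupuncture arm alone is significant with probability p(1 − p), and exactly one arm with 2p(1 − p).

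| ρ | δ (SD) | p | Acupuncture arm only | Exactly one arm |
|---|---|---|---|---|
| 0.5 | 0.3 | 20% | 16% | 32% |
| 0.5 | 0.5 | 47% | 25% | 50% |
| 0.5 | 0.7 | 75% | 19% | 38% |
| 0.7 | 0.3 | 31% | 21% | 42% |
| 0.7 | 0.5 | 68% | 22% | 44% |
| 0.7 | 0.7 | 92% | 7% | 14% |

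These are rates per index; the article lists several MRI indices.

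**5. Comparing change without a baseline covariate.** The variance factor is 2(1 − ρ), with 30 degrees of freedom. Power at 0.8 SD is 46%, 59%, 81% and 93% at ρ = 0.3, 0.5, 0.7 and 0.8. Below ρ = 0.5 this is less precise than the week-2 test; ANCOVA is at least as precise as either, apart from the one degree of freedom.

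**The case against.** The strongest reply is that the stated between-arm test is sound. Under 1:1 randomisation a week-2 t-test is unbiased and keeps its nominal error rate, and chance imbalance is already reflected in its standard error. That stands: the fault is lost efficiency.

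A reader might infer that the protocol will claim an effect because only the acupuncture arm shows significant change. The article states no such rule. It gives a direct between-arm test next to the paired tests, and the correlation step is not a rule for claiming efficacy. The layout invites that inference but does not prescribe it.

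Other stronger readings also fail:

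- *The scales are compared on post-treatment scores only.* The time point is not named, and the paragraph opens with baseline comparisons. What can be said is that no baseline adjustment is stated.
- *Baseline is ignored.* It enters the paired tests, and baseline images enter the comparison with healthy people. It is absent only from the between-arm treatment comparison.
- *Person-constant covariates are useless in paired tests.* They cancel as main effects, but could be modelled as predictors of change, and the article does not assign them to those tests.

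The reply is also right that nothing in the documents supports a high correlation for MRI indices in acute stroke, and that the planned covariates may already supply some of the gain. At ρ = 0.3 the gain is only about four percentage points.

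**Conclusion.** The point holds as one of efficiency and clear inference on the primary outcome. The only randomised MRI comparison omits a covariate already collected in every patient with usable images, and change is never compared between arms. At 16 per arm and an assumed 0.8 SD, baseline adjustment raises power from about 59% to between 63% and 95% for assumed correlations of 0.3 to 0.8, less whatever the listed covariates already explain. With equal true change in both arms, the acupuncture arm alone would be significant in about 7% to 25% of trials per index (δ of 0.3 to 0.7 SD, ρ of 0.5 or 0.7). For the scales the conclusion is narrower: no baseline adjustment is stated, the time point is open, and change is tested only within arms. The documents do not support calling the planned MRI test invalid or biased.

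**What to change.** - **MRI, region level.** Make the treatment test an ANCOVA of the week-2 value on arm, the baseline value of the same index and the listed covariates.
- **MRI, voxelwise in SPM.** The baseline value differs at every voxel, so use a group-by-time or change-image comparison between arms. State that this can be less precise than the week-2 test when the correlation is below 0.5, and take the treatment estimate from the region-level model.
- **Scales.** Name week 2 as the time point and use ANCOVA on the baseline score, with an ordinal model including baseline mRS for the mRS.
- **Reporting.** Give the adjusted between-arm difference with a 95% CI.
- **Paired tests.** Label them descriptive and state that no treatment claim rests on them. State that indices for the correlation step are selected on the between-arm result, or call that step exploratory.

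The cost is one degree of freedom and an analysis amendment, which the Ethics statement requires to be reported to the Ethics Committee and registry. No new data or scans are needed. The amendment should be fixed before any unblinded analysis.
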